### Procedures and data collection

#### Evaluations

Two evaluations will be conducted at the Faculty of Nursing and Physiotherapy of the University of Salamanca. The baseline assessment will take place after recruitment and before randomisation and allocation of subjects to the corresponding group. The preliminary assessment documents the independent variables and the primary outcome variables of the study. Intervention variables will also be recorded in detail and various objective tests will be applied. Subsequently, after randomization, different interventions tailored to each group will be carried out.

The final evaluation will be conducted at the end of the intervention period with no time intervals between evaluations. All tests will be performed by the same investigator in a standardized manner, as detailed in S2 Table. Investigators will be trained and have more than three years of experience in geriatric assessment. Results will be communicated through individualized, personalized reports to individuals who have indicated a preference to receive updates on results and progression at the outset.

#### Description of the variables

After signing the informed consent, a clinical history and a functional and body composition assessment will be performed for everyone, regardless of the group to which they are assigned. Sociodemographic variables, variables examining functionality (which include the two main study variables) and body composition variables will therefore be recorded. All of these are detailed below:

**Sociodemographic variables**: personal data, medical history, presence of comorbidities and concomitant medication use will be collected. At the end of the interview, blood pressure will be taken.**Primary variables**: the tests used to establish that the person has probable sarcopenia or sarcopenia probable according to the EWGSOP2 will be chosen:
Five-Repetition-Sit-To-Stand Test (5STS): this is a functional test that assesses a person’s ability to stand up and sit down from a chair for five times without using the arms (lower extremity strength). The 5STS has been shown to be a more sensitive and specific measure than the original test [33]. It also offers excellent test-retest reliability (0.89) [34].Hand grip test (HG): is a quick, easy and inexpensive test that measures hand grip strength. This test is recognized in clinical practice and in the literature as a standard instrument for measuring HG [15]. It will be performed with the Jamar Plus device in standing position and with the elbow flexed to 90 degrees, which has been shown to have excellent test-retest reproducibility (r>0.80) and excellent inter-observer reliability (r = 0.98) [35, 36].**Secondary functional variables**: the Sarc-f questionnaire will be administered as a rapid diagnostic test for sarcopenia that predicts the need for further evaluation [37]. Physical activity will be monitored through the International Physical Activity Questionnaires (IPAQ) [38]. The Short Physical Performance Battery (SPPB), as it is a rapid, objective three-test physical function test that measures lower extremity strength, gait speed, and balance [39]. The Timed Up&Go (TUG), which is a predictor of frailty and falls, widely used in geriatric research to measure balance and mobility in older people [40]. Gait speed, which is a simple, objective and valid measure of human gait performance that has been used in a variety of settings and is recommended for use as a "vital sign" of health [41]. Two-minute step test to measure aerobic capacity in older adults [42]. The number of falls will also be recorded one year before the start and during the intervention.**Secondary body composition variables**: electrical bioimpedance (TANITA BC-418) will be used to measure most body composition parameters. The total percentage of fat (BF%) and muscle, which is important for general health, will be calculated [43]. Additionally, appendicular muscle mass (ASM) will be calculated, as it is one of the most important variables in the diagnosis of sarcopenia today. It is generally adjusted for height to obtain the appendicular muscle mass index (SMI) (ASM/height^2^). In order to predict the risk of developing chronic diseases, measurements of visceral fat, waist circumference (WC), and body mass index (BMI) (weight/height^2^) will be taken [15]. Height will be measured with a height rod.

All these outcome variables will be measured at baseline and at the end to check the change after the different interventions.

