#### Interventions

All study participants will continue with their medical treatment guidelines, level of physical activity, and dietary pattern. Two parallel intervention programs will be designed; the control group will not receive any intervention. The exercise sessions, which will be conducted by healthcare professionals with more than one year’s experience in providing exercise sessions for older adults, will be held at senior centres throughout the city. Adherence to the program will be verified by daily attendance at exercise sessions.

The PT and MT sessions will follow the ACSM recommendations and the basic principles of the FITT-VP (frequency, intensity, type of exercise, time, volume and progression) are followed [44]. There will be three 50-minute sessions per week for 32 weeks. The sessions will begin and end with common exercises, starting with active mobility and ending with stretching and diaphragmatic breathing. The load progression will be based on individual perceived exertion. At the end of each week, participants will be asked to rate their perceived exertion using the modified Borg scale. If the score is less than 7, the intensity of the exercises will be increased for the following week to maintain a consistent level of 7 on the scale. The experienced health personnel delivering the sessions will determine how to progress, such as increasing external weight, repetitions, sets, reducing rest time, or performing unilateral exercises. Although these are group sessions, progression and volume will be adjusted on an individual basis, due to the variability of comorbidities that older adults may present.

The rooms in the senior centres for the interventions will maintain a uniformity in their infrastructure, ensuring in all cases an environment conducive to the optimal realization of the intervention sessions. To encourage adherence, attendance will be collected for each session. If they do not attend, they will be called to their attention, even warning that they may be excluded. Although the number and duration of sessions will be identical in both groups, the nature of the intervention will be different for each study group, and participants will remain unaware of their assignment to a specific group.

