**Power training (PT):** The objective of this group is to perform the strength exercises at high speeds. To avoid and minimize the possible risks that older adults may have and to have 8 months of intervention, a correct progression of the load will be carried out. A series of simple exercises with little material will be proposed. They will be based on lower limb exercises (squat, deadlift, front and sagittal lunges, hip extensions and abductions and heel raises) and upper limb exercises (wall push-ups, arm raises, elbow push-ups and extensions). We have tried to design a simple and low-cost exercise program with the objective that the participants will continue to perform it once they finish the study. The exercises, the phases of the program, the objectives and the ways to progress can be seen in Table 1. The exercises, the phases of the programme, the objectives and the ways of progressing can be seen in Table 1.**Multicomponent training (MT)**: it will include different modalities of moderate-intensity physical activity. During the session, aerobic, active mobility, strength, balance and coordination exercises will be integrated as shown in Table 2.**Control group (CG):** participants in this group should continue with their usual dietary pattern and level of physical activity, without modifying their lifestyle habits during the study period. They will not participate in any of the two programmes, they will not be able to do physical exercise in a systematic and programmed way in any other programme.

**Table 1 pone.0313072.t001:** Exercise and phases of the power exercise program.

**UPPER LIMB EXERCISES**			**LOWER LIMB EXERCISES**	
Wall push-ups, arm raises, elbow push-ups and extensions.			Squat, deadlift, front and sagittal lunges, leg extensions, hip extensions and abductions and heel raises.	
**Target phase**	**Objetives**	**Types of contraction**		**How to progress**
**1st phase: Adaptation to the exercise (1st month)**	Teach correct execution of resistance exercise patterns.	Isometric exercises and very controlled isotonic contractions.		Increase isometric contraction times, range of motion, remove supports, etc.
**2nd phase: resistance training (2nd-3rd month)**	Progress in resistance exercises.	Isotonic exercises (concentric, eccentric) at low and normal speeds.		Increase the number of repetitions per set, the number of sets or the external weight, progress towards unilateralism, decrease rest time between sets, etc.

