### Data analysis

Statistical analysis will be performed using an intention-to-treat (ITT) approach. Baseline differences between groups will be tested using normality plots and the Kolmogorov-Smirnov test. Homogeneity between groups will be assessed using Levene’s test, thus ensuring successful randomisation. Missing data will be handled using the imputation method of the last observation carried forward. It will be decided to keep outliers in the analysis, as they may represent legitimate outliers or relevant information, which will be discussed in the future study.

A descriptive analysis of the dependent and independent variables of each group will be carried out. Quantitative variables will be expressed as mean ± standard deviation, while qualitative variables will be presented as frequency distributions and percentages.

To assess the effect of the interventions on the study variables in each group, multivariate analysis of variance (MANOVA) will be used as the main method. The variables will be grouped into two large blocks: those measuring functionality (HG, 5STS, GS, TUG, Two-minute step test and SPPB) and those measuring body composition (weight, WC, BF%, visceral fat, ASM, SMI and BMI). Subsequently, MANOVA will be performed on the difference in means after the intervention, using time as an intra-group factor and type of intervention as an inter-group factor. To graphically represent the MANOVA, the canonical Biplot will be displayed, including the confidence circles representing the set of variables in each intervention group. If the circles do not overlap, it can be concluded that there are significant differences between the groups.

To verify the results of the MANOVA, differences between groups for each quantitative variable, both functional and body composition, will be analysed using the repeated measures univariate analysis of variance (ANOVA) test for normal and homogeneous variables or the Kruskal-Wallis test for non-normal or heterogeneous variables. As an additional method, pairwise comparisons will be performed using Bonferroni’s test for normal and homogeneous variables and Dunn’s test for non-normal and heterogeneous variables to determine between which groups there are significant differences.

The effect size in ANOVA of the results obtained in each group will be measured by eta squared (η^2^). Values around 0.01 indicate a small effect size, around 0.06 a medium effect size, and 0.14 or more a large effect size.

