## Discussion

The study aims to investigate the impact of PT on older women at risk of sarcopenia. It is hypothesized that PT can reverse the probable sarcopenic state in women over 65 years of age, acting as an effective preventive therapy that eliminates the risk of sarcopenia and prevents its associated factors. Additionally, it is hypothesized that PT will significantly enhance functionality and body composition in comparison to other forms of exercise and no physical activity.

It is important to note that sarcopenia, which is commonly associated with frailty, is also independently linked to an increased risk of falls [45, 46]. By preventing sarcopenia, hospitalizations, institutionalizations, and other associated adverse effects can be indirectly avoided. The scientific community has demonstrated with high certainty that exercise programs reduce the rate and number of falls in the elderly [47]. Therefore, we expect both PT and other forms of exercise to improve this aspect, with a particularly optimistic expectation for PT.

Meta-analyses have been conducted to evaluate the effect of PT on healthy older adults [25, 26]. Similarly, meta-analyses have been performed to assess the impact of RT on function and body composition in people with sarcopenia [15, 48, 49]. However, this study is the first of its kind to investigate older women with probable sarcopenia according to EWGSOP2 diagnostic criteria. This study aims to address a gap in scientific knowledge by investigating an understudied area. To our knowledge, only one other clinical trial has evaluated the effect of RT in older women and men with probable sarcopenia. However, this trial only assessed appendicular lean mass and BF% [50].

This study investigates the effect of PT as a preventive treatment in older women with probable sarcopenia. It represents an important advancement in understanding and addressing this condition, as scientific evidence on the various forms of preventive treatment available for sarcopenia has been insufficient. However, this study’s findings will not only fill the knowledge gap but also support the recommendations issued by the EWGSOP2 in 2019. This will provide a solid basis for implementing effective prevention and treatment strategies for sarcopenia in older women [15].

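### Falls are counted over 52 weeks before and about 32 weeks during the intervention, so the raw count drops by about 38% in every arm with no effect

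*Protocol article*

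**What the plan says.** The protocol article lists falls among the secondary functional variables (Description of the variables): "The number of falls will also be recorded one year before the start and during the intervention". The earlier window is therefore 12 months. The later window is the intervention, whose length is given in Interventions: "There will be three 50-minute sessions per week for 32 weeks". The same section also describes it in months: "to have 8 months of intervention". Under Evaluations, "The final evaluation will be conducted at the end of the intervention period", so nothing extends the second window to a year.

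Description of the variables closes with a sentence that covers every outcome, falls included: "All these outcome variables will be measured at baseline and at the end to check the change after the different interventions".

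Data analysis then states that "differences between groups for each quantitative variable, both functional and body composition, will be analysed using the repeated measures univariate analysis of variance", with Kruskal-Wallis as the alternative for variables that are not normal or not homogeneous. It also imputes missing data by last observation carried forward (LOCF). No section expresses falls as a rate or adjusts for observation time.

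On falls, the Discussion says "we expect both PT and other forms of exercise to improve this aspect" and is most optimistic about power training.

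**The concern.** A count from a 52-week window and a count from a 32-week window are not on the same scale. If their difference is taken as the change in falls, part of it is the difference in window length, and it appears whether or not anyone falls less often.

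Two results are at stake. The first is any statement that falls decreased within an arm or over time. Data analysis sets out to assess effects in each group and uses time as a within-group factor, and the Discussion expects both exercise arms to improve on falls, so a drop produced by the windows could be read as confirmation. The second is the handling of dropouts. There are only two evaluations, so the only value available to carry forward is the count for the previous 12 months, which would then stand in for the 32 intervention weeks.

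**Working it through.** The protocol gives no fall rate, expected reduction or power for falls, so there is no stated figure to reproduce.

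**Inputs from the protocol article**
- Window before: 1 year = 52 weeks (Description of the variables).
- Window during: 32 weeks, also described as 8 months (Interventions).
- Expected loss to follow-up: 20%; 105 women allocated 1:1:1, so 35 per arm, or 28 after losses (Sample size).

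**Assumption.** Each woman's fall rate λ (falls per year) is constant and treatment has no effect. The percentages below do not depend on λ.

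**1. Completers**
- Expected count before: λ. Expected count during: λ × 32/52 = 0.615λ.
- Apparent reduction: 1 − 32/52 = 38.5%.
- Read as 8 of 12 months: 1 − 8/12 = 33.3%.

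**2. Dropouts under LOCF**
- Imputed count λ against expected count 0.615λ: ratio 52/32 = 1.63.
- A dropout shows zero change. With 20% dropouts who have the same fall rate as completers, the apparent reduction in the whole arm is 0.8 × 38.5% = 30.8%.

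**3. Effect of unequal losses on the between-arm contrast**
- Expected raw change in an arm with loss fraction d: −λ(1 − d)(20/52).
- Difference between two arms: λ(d₁ − d₂)(20/52). It is zero when losses are equal, and the arm that loses more shows the smaller apparent reduction.
- Example, 20% against 0% losses: 0.2 × 0.385 × λ = 0.077λ, or 0.02, 0.04 and 0.08 falls per woman at assumed rates of 0.3, 0.5 and 1.0 per year.

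**4. Simulation under no effect, complete follow-up.** Three arms, gamma-Poisson counts (gamma shape 1), 10,000 trials per setting, two-sided 5% tests. The fall rates are assumptions. The columns give the proportion of trials declared significant.

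| Falls/year | n per arm | Change within one arm | Overall time effect | Time effect, annualised counts | Group-by-time |
|---|---|---|---|---|---|
| 0.3 | 28 | 0.109 | 0.308 | 0.050 | 0.046 |
| 0.3 | 35 | 0.141 | 0.384 | 0.052 | 0.050 |
| 0.5 | 28 | 0.169 | 0.477 | 0.050 | 0.047 |
| 0.5 | 35 | 0.209 | 0.571 | 0.046 | 0.046 |
| 1.0 | 28 | 0.299 | 0.765 | 0.048 | 0.045 |
| 1.0 | 35 | 0.382 | 0.860 | 0.051 | 0.049 |

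The simulated reduction was 38.2% to 38.5% at every rate. With raw counts the time effect is falsely significant in 31% to 86% of trials. Scaling the intervention count by 52/32 brings it back to about 5%. The group-by-time test stays at 4.5% to 5.0% throughout.

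**The case against.** **The falls analysis is not spelled out.** The MANOVA functional block is "those measuring functionality (HG, 5STS, GS, TUG, Two-minute step test and SPPB", without falls, and the univariate tests are introduced as a check on the MANOVA. The sentence on change is generic, and an analysis plan that is not shown could use a rate. This limits how firmly the point can be put: the article does not name a falls model. What stands is that falls are listed as a functional variable, the general sentence includes them, and the only univariate methods named have no exposure term. The two windows themselves are fixed by the text.

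**The time effect may never be tested on falls.** Fall counts in about 30 women per arm are unlikely to be normal, so they would probably go to Kruskal-Wallis, which compares groups and has no time factor. This is fair. The 31% to 86% figures apply only if the repeated-measures ANOVA is used. The 38% drop in the raw means does not depend on the test and would remain in any descriptive before/after figure.

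**The main comparison is between arms.** This also stands. All arms share both windows, so a reader who infers that they favour power training over the other arms goes further than the documents allow: a no-exercise arm with complete follow-up would show the same drop.

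**Chance imbalance.** A reader might add that an arm with more falls beforehand automatically shows more falls prevented. For a gap of 0.5 falls per year that would be 0.5 × 20/52 = 0.19 falls. The gap is an illustration with no source in the protocol, and under randomisation its expected value is zero.

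**LOCF works against the artefact.** Dropouts show no change, which shrinks the apparent reduction. If the exercise arms lost more women, the control arm would show the larger drop. It therefore cannot be said that the error as a whole leans towards the hypothesis.

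**Conclusion.** The concern holds for before/after change and, conditionally, for missing data.

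- Followed as written, the raw fall count drops by about 38% among completers in every arm with no effect (33% on the 8-month reading; about 31% overall with 20% losses and LOCF). A within-arm or time effect on raw counts would be spurious. The percentages rest on a constant fall rate and are expectations, around which a single trial will vary.
- With complete follow-up the windows do not bias the comparison between arms.
- With LOCF, each dropout is given 1.63 times her expected intervention-period count. The contrast between arms is distorted only if losses differ by arm, and the direction depends on which arm loses more. Equal losses cannot be taken for granted, because the attendance criterion for elimination can apply only where there are sessions.

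Falls are a secondary outcome, and the primary variables are unaffected. The change should still be made, because the Discussion draws an expectation about falls and the correction is simple.

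**What to change.** State in Data analysis that:

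1. Arms are compared on falls during the intervention, as a rate per person-time. A count model serves (Poisson with robust errors, or negative binomial), with log follow-up time as offset, arm as factor and the prior-year fall count as covariate.
2. Centre is accounted for as far as the number of centres allows. If all 105 women come in groups of 5 to 15, there are between 105/15 = 7 and 105/5 = 21 groups over three arms, so an elaborate cluster model may be unstable.
3. Any before/after figures for falls are given per person-year.
4. Falls are excluded from LOCF and from the raw-change tests. A woman who leaves early contributes the time for which she was observed.

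The cost is mainly wording. The one practical demand is that follow-up time be taken from final-visit or withdrawal dates in all three arms, because control participants have no session attendance from which to derive it. Those dates, and falls up to withdrawal, need to be recorded prospectively.

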#### Interventions

All study participants will continue with their medical treatment guidelines, level of physical activity, and dietary pattern. Two parallel intervention programs will be designed; the control group will not receive any intervention. The exercise sessions, which will be conducted by healthcare professionals with more than one year’s experience in providing exercise sessions for older adults, will be held at senior centres throughout the city. Adherence to the program will be verified by daily attendance at exercise sessions.

The PT and MT sessions will follow the ACSM recommendations and the basic principles of the FITT-VP (frequency, intensity, type of exercise, time, volume and progression) are followed [44]. There will be three 50-minute sessions per week for 32 weeks. The sessions will begin and end with common exercises, starting with active mobility and ending with stretching and diaphragmatic breathing. The load progression will be based on individual perceived exertion. At the end of each week, participants will be asked to rate their perceived exertion using the modified Borg scale. If the score is less than 7, the intensity of the exercises will be increased for the following week to maintain a consistent level of 7 on the scale. The experienced health personnel delivering the sessions will determine how to progress, such as increasing external weight, repetitions, sets, reducing rest time, or performing unilateral exercises. Although these are group sessions, progression and volume will be adjusted on an individual basis, due to the variability of comorbidities that older adults may present.

The rooms in the senior centres for the interventions will maintain a uniformity in their infrastructure, ensuring in all cases an environment conducive to the optimal realization of the intervention sessions. To encourage adherence, attendance will be collected for each session. If they do not attend, they will be called to their attention, even warning that they may be excluded. Although the number and duration of sessions will be identical in both groups, the nature of the intervention will be different for each study group, and participants will remain unaware of their assignment to a specific group.

**Power training (PT):** The objective of this group is to perform the strength exercises at high speeds. To avoid and minimize the possible risks that older adults may have and to have 8 months of intervention, a correct progression of the load will be carried out. A series of simple exercises with little material will be proposed. They will be based on lower limb exercises (squat, deadlift, front and sagittal lunges, hip extensions and abductions and heel raises) and upper limb exercises (wall push-ups, arm raises, elbow push-ups and extensions). We have tried to design a simple and low-cost exercise program with the objective that the participants will continue to perform it once they finish the study. The exercises, the phases of the program, the objectives and the ways to progress can be seen in Table 1. The exercises, the phases of the programme, the objectives and the ways of progressing can be seen in Table 1.**Multicomponent training (MT)**: it will include different modalities of moderate-intensity physical activity. During the session, aerobic, active mobility, strength, balance and coordination exercises will be integrated as shown in Table 2.**Control group (CG):** participants in this group should continue with their usual dietary pattern and level of physical activity, without modifying their lifestyle habits during the study period. They will not participate in any of the two programmes, they will not be able to do physical exercise in a systematic and programmed way in any other programme.

**Table 1 pone.0313072.t001:** Exercise and phases of the power exercise program.

**UPPER LIMB EXERCISES**			**LOWER LIMB EXERCISES**	
Wall push-ups, arm raises, elbow push-ups and extensions.			Squat, deadlift, front and sagittal lunges, leg extensions, hip extensions and abductions and heel raises.	
**Target phase**	**Objetives**	**Types of contraction**		**How to progress**
**1st phase: Adaptation to the exercise (1st month)**	Teach correct execution of resistance exercise patterns.	Isometric exercises and very controlled isotonic contractions.		Increase isometric contraction times, range of motion, remove supports, etc.
**2nd phase: resistance training (2nd-3rd month)**	Progress in resistance exercises.	Isotonic exercises (concentric, eccentric) at low and normal speeds.		Increase the number of repetitions per set, the number of sets or the external weight, progress towards unilateralism, decrease rest time between sets, etc.
**3rd phase: high-speed resistance training (4th-8th month)**	Gain muscle power.	Isotonic exercises progressively increasing the speed of the concentric phase.		Increase the speed of the concentric contraction and the number of repetitions at maximum speed. Subsequently, the number of series will be increased, external weight will be added or progress towards unilateral at maximum speed.

**Table 2 pone.0313072.t002:** Sample session of the principal part of multicomponent training.

EXERCISE COMPONENT	EXERCISES	FORM OF PROGRESSION
**AEROBIC EXERCISE 10´**	Walking, running.	Increases in continuous walking speed, progress to running start, increases in pace, intervallic work, progressive decrease in rest.
**RESISTANCE EXERCISE 10´**	Upper and lower limb isotonic exercises.	Increase number of repetitions per set, number of sets, progress towards unilateral, decrease rest time between sets.
**COORDINATION AND BALANCE 10´**	Balance exercises, dual task and coordination of upper and lower limb.	Progress by disturbing vestibular system, visual, monopodal support, imbalances, unstable surface, complication of dual-task exercises, more complicated and faster decision making, etc.

